### Provider-related utilisation: care manager survey

The care manager survey is intended for documenting the resource use following the services provided by the care managers. This requires each care manager to record the time spent on the various activities that comprise the BCC intervention. For example, the survey covers time spent on patient contact, organisation of treatment schedules and follow-up, collaboration with general practitioners, specialists, and informal carers, as well as other organisational and administrative tasks. The survey will take place over a period of four weeks and spread over different time points at all participating sites. This approach aims to neutralise potential seasonal effects and variation within patient cohorts, as well as to incorporate provider learning and scale effects [32]. In addition to the primary care manager survey, a short supplementary questionnaire will be administered to the local trainers of care managers in each country. This supplementary questionnaire is designed to capture the time spent on tasks related to training, educational initiatives, and the regular case review meetings conducted for supervision purposes. The questionnaires have been developed and subjected to pre-testing (see Additional file 1). In addition, imergo® e-health ICP data on the number and duration of care management contacts will be used.

### Medical costs and costs of providing the intervention

To facilitate a later implementation of BCC in practice, costs will be categorised into (i) those associated with the resource use and treatment of patients in the ECAPE intervention and (ii) those associated with the provision and maintenance of the intervention. Costs associated with patient resource use and treatment will be collected through iMCQ and/or health insurance data or flat rates for services. In Germany where claims data on patients’ medical costs will be available, these sources will be used to further corroborate the information obtained from the questionnaires, such as the iMCQ. This dual approach ensures data validation and should increase the accuracy and reliability of the economic evaluation. In Germany, patient receipts (based on Sect. 305 SGB V) include information on the services patients have received and the corresponding costs. German health insurance funds are obliged to provide these receipts to insured individuals, upon request. The participant signs an additional informed consent form that legally authorises the study staff to request data from health insurance companies. The subsequent data request and delivery process between the study team and the health insurance companies for all German sites will be centrally coordinated by the study centre in Göttingen in accordance with national regulations and data protection laws. Statutory health insurance (SHI) access is likely to be feasible mainly in Germany. Where cross-country comparisons are possible, results are converted into a common currency using purchasing power parity adjustments in order to account for differences in the cost of goods and services across countries [33].

The costs related to the provision of the intervention will reflect the resource use associated with the BCC intervention, i.e., costs related to the time spent by care managers, costs due to training and those of supervision. In addition, the costs of information and education materials for patients and their informal carers and the costs associated with the technological support (including the imergo® e-health ICP, network websites and interactive, multilingual patient websites) will also be considered.

Figure 2 provides a detailed overview of the intended structure of the economic evaluation, including the outcome measures, and the identification of resource use and costs.

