### Resource use and costs

Data on resource use and costs associated with the BCC intervention will be obtained from multiple sources and standardised approaches, as the feasibility of accessing medical records and the costs vary from country to country. The imergo® e-health Integrated Care Platform (ICP) will be used to collect study-related medical information and to further enhance the data collection process for patients assigned to the intervention group throughout the study. Patient-related and provider-related utilisation will be measured by applying a time-driven activity-based costing (TDABC) approach [26]. The TDABC will streamline the care process by focusing on the time required to execute activities along the care pathway. Corresponding costs will be assigned to specific activities by multiplying the time invested in an activity by the corresponding capacity cost rate of the resources involved [27–30]. Table 1 provides an overview of possible methods for collecting costs and resources.

**Table 1 Tab1:** Potential methods for collecting costs and resources

Sites	Patient-related		Provider- and study-related	
	Health insurance data (utilisation and costs)	Medical consumption (only utilisation)	imergo® e-health ICP (study-related medical records and assessments)	Care manager survey (provider-related resources)
Germany	Patient receipts	-	x	x
Denmark	Possible	iMCQ	x	x
Italy	tbd	iMCQ	x	x
Lithuania	tbd	iMCQ	x	x
Hungary	tbd	iMCQ	x	x

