### Patient-related utilisation: medical consumption questionnaire (iMCQ)

Patient-related resource utilisation will be assessed using the iMCQ, medical records and study data retrieved from the external clinical information system secuTrial and the imergo® e-health ICP. The iMCQ will cover all healthcare services provided to individual patients which are not part of the intervention. In order to reduce the participants’ burden of study-specific processes, questions of limited relevance were excluded in accordance with the prescribed questionnaire guidelines [31]. Similarly, the medication chart has been adapted as the task of documenting medication details will be entrusted to the care managers. The iMCQ will be administered at the start of the RCT, at the 9-month point (i.e., end of treatment), and at the ≥ 18-month milestone (i.e., end of study). The retrospective iMCQ will record the patient’s medical consumption over the last 3 months. As it is not feasible to administer the iMCQ quarterly, patient-related utilisation will be determined based on available evidence and agreed upon by clinical experts. Resource utilisation will be extrapolated to the 9-month intervention or 18 to 33-month follow-up period. The iMCQ will not be implemented in Germany, as patient receipts cover costs and medical consumption.

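### The plan says German claims data will validate the iMCQ, but the iMCQ is not used in Germany, so that check cannot take place and cost source is largely tied to country

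*Protocol article*

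**What the plan says.** Three places in the protocol article bear on this.

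- **Medical costs and costs of providing the intervention.** For Germany, where claims data are expected, "these sources will be used to further corroborate the information obtained from the questionnaires, such as the iMCQ". The next sentence draws the benefit: "This dual approach ensures data validation and should increase the accuracy and reliability of the economic evaluation". The same section expects insurer data from few other places: "Statutory health insurance (SHI) access is likely to be feasible mainly in Germany".
- **Patient-related utilisation: medical consumption questionnaire (iMCQ).** "The iMCQ will not be implemented in Germany, as patient receipts cover costs and medical consumption". Elsewhere the questionnaire looks back three months and is given at baseline, at 9 months and at 18 months or later. Use outside those windows is extrapolated.
- **Table 1, under Resource use and costs.** The German row reads "Germany Patient receipts - x x", with the dash in the medical consumption column. The Danish row reads "Denmark Possible iMCQ x x". Italy, Lithuania and Hungary also have the iMCQ, with insurance data still to be determined.

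**The concern.** The medical costs section credits the cost data with a validity check that the rest of the article rules out. This matters because the iMCQ is the source that most needs checking: it is self-report over a short window, stretched over a much longer period with the help of outside evidence and expert agreement. Comparing it with insurer records in the same patients is the only check on it that the article describes.

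The second consequence is for comparison across countries. The article aims at cross-country cost-effectiveness and cost-utility results and at transferring findings between jurisdictions. If one country is measured by insurer records and four mainly by extrapolated recall, with no assured group of patients measured both ways, a difference in cost level between Germany and the rest may reflect the country, the method or both. The purchasing power adjustment deals with prices. The bootstrap deals with sampling error. Neither addresses a systematic difference between sources.

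**Working it through.** The plan gives no figure to reproduce, so the check compares the statements and then sizes the consequence with simple ratios.

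**Step 1: which country has which source** (Table 1 and the two sections above)

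| Country | Insurer data | iMCQ | Both in the same patients? |
|---|---|---|---|
| Germany | Patient receipts | No | No |
| Denmark | Possible | Yes | Only if insurer data are obtained |
| Italy, Lithuania, Hungary | Undecided | Yes | Undecided |

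German patients with both claims and iMCQ: 0. The statement that claims corroborate the iMCQ in Germany and the statement that the iMCQ is not used there cannot both be true. The only country with a definite insurer source has no questionnaire, and the four with the questionnaire have no definite insurer source.

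**Step 2: how much time the iMCQ observes**

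Inputs: a recall window of 3 months, an intervention period of 9 months, and total follow-up of 18 to 33 months. The baseline window lies before randomisation and does not count.

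- Intervention period, one window: 3/9 = 33%.
- Total follow-up, two post-baseline windows: 6/18 = 33% at the shortest, 6/33 = 18% at the longest.

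The remaining 67% to 82% of the time is extrapolated. German receipts could cover the whole period, on the assumption that they are requested for all of it.

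**Step 3: how many patients are on each side**

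The section on study design gives 150 per group, so 300 in total, and country targets from 33 to 124. Germany's own target is not stated. Within that range:

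- Germany: 33/300 = 11% to 124/300 = 41%.
- The other four countries: 59% to 89%, relying on the iMCQ without an assured second source.

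**Step 4: what the difference in source does to the estimates**

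Suppose the main source in country *c* records a fraction *k* of true cost, the same in both arms (an assumption; the article gives no value for *k*).

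- Within country *c*, the observed cost difference between arms is *k* times the true difference. Its sign is kept and its size is scaled.
- Between countries, the observed difference in cost level is *k*₁ × cost₁ − *k*₂ × cost₂. If *k*₁ and *k*₂ differ, this can be non-zero even when true costs are equal.

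So the problem falls mainly on cross-country comparison and on pooling of cost levels. Separating *k* from country needs patients measured by both sources, and in Germany there are none.

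**The case against.** The strongest defence has three parts.

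1. **The sentence carries little weight.** The claims data are said only to corroborate further and to be expected to improve accuracy. No ratio, bootstrap or subgroup analysis takes the validation as an input, so deleting the sentence would change no described analysis. This is fair, but the article also says that the dual approach ensures validation, and a reader would rely on that when judging the cost results.

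2. **The inconsistency between countries is disclosed.** The Discussion names uncertainty about consistent cost data across the five countries as one of two major limitations, and cross-country comparison is made conditional on being possible. This stands as partial acknowledgement. It does not withdraw the German validation claim.

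3. **Leaving out the German iMCQ was deliberate.** Receipts are said to cover both costs and consumption, and the questionnaire was trimmed to limit patient burden. That is a legitimate choice. The error lies in claiming a validation that the choice excludes.

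Three stronger readings are tempting, and the documents do not support them.

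- *German patients without receipts have no utilisation data and leave the cost analysis.* Receipts do depend on a further consent ("The participant signs an additional informed consent form that legally authorises the study staff to request data from health insurance companies"), so some may be missing, and no German substitute is named. But other sources are listed without restriction to non-German sites ("Patient-related resource utilisation will be assessed using the iMCQ, medical records and study data retrieved from the external clinical information system secuTrial"), and flat rates are mentioned as well. Handling of missing receipts is also detail that an article commonly leaves to the full protocol or analysis plan. The article gives no basis for a count of such patients.
- *The comparison of treatment arms is confounded by data source.* In Table 1 both arms within a country share the same main source.
- *No overlap can arise anywhere.* Denmark is listed as possible and three countries are undecided.

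**Conclusion.** The concern holds as an internal contradiction with a practical consequence. As written, the validation of questionnaire data by claims cannot take place in Germany, the country to which it is assigned: no German patient has both sources. An overlap elsewhere is possible or undecided, and none is planned as validation.

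The consequence is that cross-country comparison and pooling of cost levels mix country with measurement method. On one side are insurer receipts for 11% to 41% of patients. On the other, for 59% to 89%, is recall that directly observes 33% of the intervention period and 33% to 18% of total follow-up. The patient shares rest on Germany's unstated target lying within the published range. The direction and size of any resulting bias cannot be worked out from the article. The within-country contrast between arms is less affected, provided that each source captures costs equally well in both arms.

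This is a statement that is wrong as written, not detail left to another document.

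**What to change.** Reconcile Table 1, the iMCQ section and the medical costs section as follows.

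1. Withdraw the claim that claims data corroborate the iMCQ in Germany and that a dual approach ensures validation there. State that German utilisation comes from receipts.
2. Assign the comparison of iMCQ with claims to Denmark, or to any other country where insurance data are obtained. If none is obtained, say that the iMCQ was not validated in this study.
3. Estimate incremental costs within country first and then pool. Add a sensitivity analysis by data source, for example with and without Germany. This shows how far the pooled result depends on the source; because it removes a country and a method together, it cannot tell them apart.

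These steps need only wording and analysis, with no new data collection.

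Optionally, give the reduced iMCQ at the German visits still to come. This would create the overlap that the text promises and would allow the two sources to be compared in the same patients. It costs an amendment and a minor burden on patients. The first patient was randomised in July 2022, so visits already passed cannot be recovered and the overlap would be partial.

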**Fig. 2 Fig2:**
[figure not shown]
Planned economic evaluation in the ESCAPE study including data collection measures

### Uncertainty and validity

Addressing uncertainty in economic evaluations is crucial for enhancing the credibility of findings. Sensitivity analyses provide transparency about the robustness of the results, helps decision-makers to understand the potential variability in outcomes, and enables informed decisions by considering the range of possible scenarios and their associated risks and benefits. Bootstrap nonparametric resampling will be used to account for uncertainty in the analyses [34]. It allows drawing samples with replacement from the original data for calculating the parameter of interest repeatedly. This generates a vector of bootstrap replicates, serving as an empirical estimate of the statistic’s sampling distribution. Repeating this process numerous times (at least 1000 times for confidence intervals) generates the empirical distribution of cost-effectiveness [34]. The results will be presented using cost-effectiveness planes and cost-effectiveness acceptability curves (CEAC). The cost-effectiveness plane serves as a visual representation, highlighting random values of both incremental cost and effects. The CEAC provides the probability of cost-effectiveness of the intervention across a range of willingness-to-pay thresholds [35]. CEACs allow decision-makers to calibrate their judgements across different financial thresholds.

To strengthen the internal and external validity of this study, the Consolidated Health Economic Evaluation Reporting Standards 2022 (CHEERS2022) statement will be followed [36].

### Subgroup analyses

All outcome measures, i.e., EQ-5D-5L, HADS and KCCQ-12, will be assessed in all patients at three time points (baseline, end of treatment and end of study). Additional subgroup analyses for patients with depressive and cardiovascular symptoms will be performed (see Table 2). For patients with cardiovascular symptoms (e.g., shortness of breath, fatigue), the KCCQ-12 will identify subgroups related to symptom severity. Subgroup analyses will be performed based on scores less than 75 (very poor to good) and 75 to 100 (good to excellent) [37, 38].

DFDs will be calculated for patients with a score of 8 or higher on the HADS depression subscale to identify patients with depressive symptoms [39]. For the HADS total scale, the cut-off will be 15 and above [40]. HADS scores will be converted to DFD using linear interpolation. This method has been used in previous studies, for example with the Hopkins Symptom Checklist (HSCL) [7, 19, 41]: Over the course of a follow-up period, patients were assigned an appropriate DFD value for each day. To estimate the DFD value, scores of the HSCL that are equal to or less than 0.50 were attributed one DFD, scores of 1.7 or greater were assigned zero DFDs, and scores between 0.50 and 1.7 were assigned DFD values ranging from 0 to 1 by linear interpolation. For example, an HSCL-20 score of 1.1 corresponds to 0.5 DFD [41]. It is noteworthy that these thresholds values have been validated by previous research (i.e. correlation with the Hamilton Rating Scale-Depression (HRS-D) scores or the Beck Depression Inventory (BDI)) [42, 43]. However, until now there has been no formula for converting measures of severity of disease-specific symptoms (e.g., a patient’s psychological distress) using the HADS. As part of this analysis, a formula, and thresholds for converting the HADS to DFDs will be developed and defined. In addition, DFDs can be used to validate QALYs. This approach is based on the rationale that depression is equivalent to a 0.2–0.4 reduction in QALY weights, so that 1 year of depression is effectively equivalent to an equivalent reduction in QALYs [43–45].

**Table 2 Tab2:** Overview of outcome measures and subgroup analyses

Type of analysis	Questionnaire	Endpoints		Characteristics of subgroup
		All Patients	Subgroup	
**Cost-effectiveness analysis** **(CEA)**	KCCQ-12	Hospital admissions avoided	Hospital admissions avoided	Cardiovascular symptoms as measured by the KCCQ-12 with a cut-off score ≤ 74.
	HADS	-	Depression-free days	Depressive symptoms as measured by the depression subscale of the HADS at a cut-off of ≥ 8 and for the HADS total score at ≥ 15.
**Cost-utility** **analysis** **(CUA)**	EQ-5D-5L	QALYs	-	-

## Discussion

This study protocol presents a comprehensive design for the health economic evaluation of a BCC intervention for elderly, multimorbid HF patients. By exploring the economic dimensions, this evaluation aims to provide insights into the practical feasibility, cost-effectiveness, and wider implications of implementing BCC intervention to elderly multimorbid HF patients across Europe.

One strength of this study is that the economic analysis will be based on various methods and approaches. For example, the integration of a TDABC approach enables an accurate identification of cost drivers by directing attention towards time. This direct alignment between cost and activity duration not only facilitates a detailed reflection of the care process but also allows for a streamlined implementation of BCC intervention in routine care contexts [27, 29]. Moreover, the TDABC has shown to be adaptable to different international health care settings [26, 29].

The economic assessment of the BCC intervention faces various methodological challenges. However, provided sufficient data, the chosen design may serve as a solid basis for the evaluation. Standardised questionnaires, including three outcome assessments, are a viable basis for assessing the quality of life and resource use of patients with HF receiving BCC.

Although our economic approach for evaluating BCC will be based on a variety of methodologies, there are two major limitations. First, as it is common for trial sample sizes to be based on the primary clinical outcome, the analysis lacks a pre-planned sample size calculation specifically for the economic aspects [33]. This could impact the statistical power of the economic evaluation (e.g., due to a higher extent of incompleteness for cost data than for clinical data). Second, the uncertainty of obtaining consistent cost data for all five European countries, and the wide variation in target recruitment numbers between countries, may weaken the robustness of the analysis. As a result, and facing the inherent uncertainties of such complex projects, partial changes to the analysis plan may be justified and unavoidable.

In conclusion, the comprehensive cross-country approach of the analysis, combined with a sophisticated manifoldness in the methods used for determining costs and outcomes, should provide a substantial starting point for a high-quality economic study on BCC intervention for older multimorbid patients. Providing the economic evaluation of ESCAPE will contribute to a country-based structural and organisational planning of BCC (e.g., the number of patients that may benefit, how many care managers are needed). The anticipated release of primary results is in 2026.

## Abbreviations

(B)CC: (Blended) collaborative care
BDI: Beck Depression Inventory
BL: Baseline
CEA: Cost-effectiveness analysis
CEAC: Cost-effectiveness acceptability curve
CHEERS: Consolidated Health Economic Evaluation Reporting Standards 2022 (CHEERS2022) Statement
CUA: Cost-utility analysis
DFD: Depression-free days
EQ-5D-5L: RQoL questionnaire w/5 dimensions developed by the EuroQol Group
ESCAPE: Evaluation of a patient-centred biopsychosocial blended collaborative care pathway for the treatment of multimorbid elderly patients
EU: European Union
FU: Follow-up
GP: General practitioner
HADS: Hospital Anxiety and Depression Scale
HRS-D: Hamilton Rating Scale-Depression
HF: Heart failure
HRQoL: Health-related quality of life
HSCL: Hopkins Symptom Checklist
ICP: Integrated care platform
ICER: Incremental cost-effectiveness ratio
iMCQ: Medical Consumption Questionnaire
ISPOR: International Society for Pharmacoeconomics and Outcomes Research
KCCQ-12: Kansas City Cardiomyopathy Questionnaire
MAM: Meta-algorithm for multimorbidity
PIC: Patient-informed consent
QoL: Quality of life
QALY: Quality-adjusted life years
RCT: Randomized controlled trial
RCT-CEA: Randomized Clinical Trials-Cost-Effectiveness Analysis
SHI: Statutory Health Insurance
TDABC: Time-driven activity-based costing
UC: Usual care
